#### Criteria for discontinuing or modifying allocated interventions {11b}

Subjects can leave the study at any time for any reason if they wish to do so without any consequences. The investigator or treating physician can decide to withdraw a subject from the study for urgent medical reasons. All interventions are personalized and can change during the follow-up period as described in the previous sections.

#### Strategies to improve adherence to interventions {11c}

Adherence is one of the primary study outcomes and thus a major focus of attention. Strategies to improve adherence include:Provision of pressure-optimized custom-made footwear for indoor use, to improve footwear adherence indoorsEducation, to emphasize the importance of the interventionPersonalization of treatments, to provide treatments specifically focused and tailored towards the participant, avoiding unnecessary proceduresDiaries, to remind participants of their checks and tasksFollow-up calls, to give feedback about measurements and adherenceMotivational interviewing, to motivate participants to improve low adherence and retain high adherence

Procedures for monitoring adherence include:Sensors (OrthoTimer; Rollerwerk, Balingen, Germany) in the participant’s custom-made (indoor) footwear, to monitor wearing time of the custom-made (indoor) footwearMeasuring physical activity levels with an activity monitor (MoveMonitor; McRoberts, the Hague, the Netherlands), to measure weight-bearing time and number of steps taken. Combined with measurements of wearing time, this generates footwear adherence.Diaries and questionnaires; to check adherence by self-reporting

#### Relevant concomitant care permitted or prohibited during the trial {11d}

All concomitant care and interventions are permitted during the trial, as long as participants meet the conditions for in- and exclusion at the time of taking informed consent.

#### Provisions for post-trial care {30}

After the participant completes the follow-up period, in-shoe pressure measurements done at the final study visit are shared with the shoe technician and physician as post-trial care. All participants receive a feedback sheet with information on measurements and outcomes throughout the study period. Participants from the enhanced therapy group may, if preferred, continue at-home foot temperature measurements. When the primary study outcomes are available after the last visit of the last participant, study results will be shared with all participants in writing.

### Outcomes {12}

There are three primary study outcomes in this study, which are:Foot ulcer recurrence during the 12-month follow-upAdherence to wearing custom-made footwearThe cost (savings) per quality-adjusted life year (QALY) gained (i.e., cost-utility)

These represent a clinical, patient-related, and health-economic perspective, respectively. Foot ulcer recurrence is defined as “a break of the skin of the foot that involves as a minimum the epidermis and part of the dermis, in a person who has a history of foot ulceration, irrespective of location and time since the previous foot ulcer” [15], is monitored during the entire study period, and is—on group level—calculated as the proportion of participants with one or more foot ulcers during the study period. Footwear adherence is defined as the percentage of steps taken in prescribed footwear, calculated by combining physical activity and wearing time measurements [44]. It is calculated over 1 week, at baseline and (for outcomes) at 6 and 12 months’ follow-up. Cost-utility is monitored during the entire study period, costs are summed throughout the 12-month period [45], and utility is scored with the EQ-5D-5L questionnaire every 3 months [46].

Secondary study outcomes are as follows: proportion of participants with one or more recurrent foot ulcers on the plantar side of the foot [15]; proportion of participants with one or more recurrent foot ulcers at the predefined personalized high-risk locations [15]; ulcer-free survival days [47]; falls [48]; wearing time of custom-made footwear [49]; in-shoe peak plantar pressure [47]; cumulative plantar tissue stress [44]; footwear wear-and-tear [50]; ulcer risk prediction score [29]; treatment and footwear satisfaction [51]; foot-related self-care [52]; knowledge of foot care [53]; capabilities, opportunities, and motivations (COM-b) score [54]; quality of life (in participants with [55, 56] or without [5] a recurrent foot ulcer during the trial); physical activity [57]; costs [45]; QALYs [46]; and cost-effectiveness [45]. In participants with an ulcer, other secondary outcomes are as follows: time to ulceration [58], ulcer severity [59–61], time to healing [58], and referral time [62]. Definitions for all secondary outcomes are as provided in the reference following each secondary outcome. All secondary outcomes are monitored during the entire study period using assessments and questionnaires during follow-up visits (see Fig. 2).

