#### Personalized treatment approach

The approach with the largest potential of helping prevent foot ulcer recurrence combines evidence-based state-of-the-art interventions as described above, integratively addressing all modalities and using a personalized approach to match an individual’s needs and preferences [27]. Such an approach requires (financial) investments. The design of pressure-optimized custom-made footwear requires investments in equipment, training of personnel, and measurement time, none of which are currently reimbursed through healthcare insurers. The provision of custom-made indoor footwear adds to the costs, as do tools to monitor footwear use and to measure at-home foot temperatures, and structured education like motivational interviewing. At-home foot temperature monitoring also requires daily assessment by the patient and possibly further diagnosis and foot care by a healthcare professional when hotspots are found. The risk of false-positive outcomes may result in over-diagnosis and treatment, adding burden to the patient and healthcare system. Finally, a multimodal state-of-the-art treatment approach likely changes the organization of care to one where more scientific, data-driven care is provided. This requires intensified collaboration within the multidisciplinary team, intensified patient monitoring, and more personalized treatment decisions based on objective data, all potentially increasing costs.

However, with the treatment of a single foot ulcer costing on average €10,000 and the reduction in quality of life of patients when having a foot ulcer [5, 6], we hypothesize that the investments required for an integrated personalized approach will be offset my substantial savings in ulcer treatment costs and thus not increase total costs for treating these people with diabetes who are at high risk of ulceration. To test this hypothesis, the cost-utility of an integrated personalized treatment approach for ulcer prevention needs to be investigated. The Diabetic Foot Assistive Devices Trial (DIASSIST) aims to assess the clinical effectiveness, patient adherence, and cost-utility of such an integrated personalized assistive devices approach to reduce the risk of foot ulcer recurrence in people with diabetes mellitus.

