#### Secondary objectives

The secondary objectives are to assess the effects of an integrated personalized assistive devices approach in people with diabetes who are at high risk of ulceration on foot ulcer recurrence on the plantar surface and at high-risk locations; ulcer-free survival days; falls; wearing time of prescribed footwear; in-shoe peak plantar pressure; cumulative plantar tissue stress; footwear wear-and-tear; ulcer risk prediction score; treatment and footwear satisfaction; foot-related self-care; knowledge of foot care; capabilities, opportunities, and motivations to perform recommended footwear behavior (COM-b) score; quality of life; physical activity; costs; quality-adjusted life years; and cost-effectiveness. For participants who develop a foot ulcer, secondary outcomes further include time to ulceration, ulcer severity, time to healing, and referral time.

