##### Assessments at baseline visit

If eligibility has been confirmed, photographs of the plantar and dorsal surfaces of both feet will be taken according to a standardized protocol [10] and foot-related self-care behavior will be assessed using a 7-item questionnaire based on a commonly used questionnaire by the Dutch Society of Podiatry (Nederlandse Vereniging voor Podotherapie, NVvP) [67]. Quality of life will be assessed by using the SF-36 and EQ-5D-5L questionnaires [5, 46]. Participants will complete a study questionnaire consisting of the following topics: satisfaction with ulcer prevention treatment; use and usability of their custom-made footwear (using a study-specified Monitor Orthopedic Footwear [51]); capabilities, opportunities, and motivations for ulcer prevention using an adapted COM-b questionnaire [54]; and knowledge of foot care (questions 24–29 from the Patient Interpretation of Neuropathy questionnaire [53]).

Furthermore, barefoot plantar pressure distribution during standing and walking will be measured using the Novel EMED-X platform system (Novel GmbH, Munich, Germany), which consists of pressure-sensing sensors (4 per cm^2^) that are sampled at 50 Hz. Four trials of both feet at the subjects’ self-chosen comfortable pace using a “two-step” gait approach to the platform will be collected [68]. In-shoe plantar pressure distribution will be measured inside the two most frequently used pairs of custom-made footwear. In-shoe pressures will be measured with the Pedar-X system (Novel GmbH, Munich, Germany), which comprises flexible pressure-sensing insoles (99 sensors, 50Hz sampling rate) placed between the sock and the shoe insole. Measurements will be performed at a self-chosen comfortable speed along a walkway of at least 10 m; gait speed will be recorded and kept within 10% for all walking trials. A minimum of 12 mid-gait steps per foot will be recorded [69].

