##### Assessments during follow-up

Each participant will be followed for 12 months. If a participant has a foot ulcer at 12 months, they will be followed for another 6 months or until healing, whichever comes first. Follow-up will take place after 3, 6, 9, and 12 months (FU3, FU5, FU7, and Final visit (FV), respectively). Prior to each regular study visit, all participants will receive the EQ-5D-5L questionnaire and study specified versions of the iMTA iMCQ and iMTA iPCQ to gather volume data on medical costs, family costs, and productivity loss [45]. Additionally, at 6 and 12 months, all participants also complete the study questionnaire (see the section “Assessments at baseline visit”), and at 12 months also the SF-36. Participants in enhanced therapy will hand in their weekly diaries.

Custom-made footwear wearing time will be assessed during each 3-monthly visit by reading out the OrthoTimer sensor in the shoe. At 6 and 12 months, physical activity is assessed by wearing the activity monitor for 1 week. At 12 months, barefoot and in-shoe plantar pressure measurements will be repeated. Use of intramural healthcare resources during the study will be obtained at final visit from the participants’ medical status. If a participant has a foot ulcer at 12 months, visits will be scheduled at 15 and 18 months, or 2 weeks after healing (whichever comes first). During these visits, volume data on medical costs, family costs, and productivity loss will be gathered (iMTA) and the EQ-5D-5L will be completed. An overview of all measurements can be seen in Fig. 2.

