##### Unscheduled assessments: foot ulceration

If the participant, treating physician, or podiatrist identifies an ulcer in-between 3-monthly regular visits, they are instructed to inform the investigator immediately, and have photographs taken of the foot by the treating physician or podiatrist. The podiatrist will debride the wound first if required to assess outcome, and will classify the ulcer using the University of Texas Wound Classification [59] and the WIfI-score [60, 61]. This information will be sent to the investigator, who will upload all information anonymously to a web-based environment for ulcer outcome assessment. A panel of blinded and independently operating physicians with > 10 years of experience in diabetic foot care will then assess these photographs. Participants will complete the validated Dutch version of the Cardiff Wound Impact Schedule [55, 56] 4 and 12 weeks after an ulcer occurred, provided the ulcer has not yet healed. Participants will complete the EQ-5D-5L one extra time, 4 weeks after an ulcer occurred, as presence of a foot ulcer is known to reduce quality of life [70]. Participants will then continue with the follow-up assessments as scheduled.

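### As worded, the SF-36 outcome is tied to participants without a recurrent ulcer, which splits a secondary outcome on the primary clinical endpoint

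*Protocol article*

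**What the plan says.** Outcomes {12} lists, among the secondary outcomes, "quality of life (in participants with [55, 56] or without [5] a recurrent foot ulcer during the trial", and adds: "Definitions for all secondary outcomes are as provided in the reference following each secondary outcome". The instruments behind the reference numbers appear elsewhere in the article:

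- Assessments at baseline visit: "Quality of life will be assessed by using the SF-36 and EQ-5D-5L questionnaires [5, 46". Outcomes {12} uses reference 46 for EQ-5D-5L, so reference 5 is SF-36.
- Unscheduled assessments: foot ulceration: "Participants will complete the validated Dutch version of the Cardiff Wound Impact Schedule [55, 56] 4 and 12 weeks after an ulcer occurred". This applies only while the ulcer is unhealed.

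Other sections treat quality of life as an outcome for the whole trial population:

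- Secondary objectives lists it without a split and only then turns to the ulcer-only outcomes: "For participants who develop a foot ulcer, secondary outcomes further include time to ulceration, ulcer severity, time to healing, and referral time".
- Assessments during follow-up says that at 6 and 12 months "all participants also complete the study questionnaire", and the same sentence continues "at 12 months also the SF-36". No ulcer-free restriction is attached.
- Statistical methods {20a} bases every between-group comparison on intention-to-treat as well as on a final-visit analysis.
- Other study outcomes tests all remaining parameters between arms by pointing back to Outcomes {12}. It gives no separate rule for SF-36.

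**The concern.** Ulcer recurrence happens after randomisation, and the intervention is designed to change it. Comparing SF-36 only among participants who stayed ulcer-free therefore compares two subsets selected by the treatment effect itself, and randomisation no longer protects that comparison.

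It also omits the pathway on which the trial's rationale rests. The section on the personalised treatment approach argues from "the reduction in quality of life of patients when having a foot ulcer". If participants with an ulcer are left out, the quality-of-life loss avoided by preventing ulcers cannot appear in the SF-36 result.

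The Cardiff schedule cannot fill the gap. It is a different scale, completed only by participants whose ulcer is still open at 4 or 12 weeks, and that group is again defined after randomisation.

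**Working it through.** **Inputs.** Expected recurrence is 37% in usual care and 15% in enhanced therapy (Sample size {14}). The total is 126, or 63 per arm (same section). The documents give no SF-36 loss per ulcer, so this loss, D (in SD units), is an assumption, shown for 0.25 to 1.0.

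**Step 1: reproduce the figure behind the rates.** Two proportions, two-sided alpha 0.05, power 80%, pooled variance under the null, mean proportion 0.26:

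n per arm = [1.960 × √(2 × 0.26 × 0.74) + 0.842 × √(0.37 × 0.63 + 0.15 × 0.85)]² / 0.22² = (1.216 + 0.505)² / 0.0484 ≈ 61.2.

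The article states 61 per arm (122 in total); rounding up gives 62 (124). The stated figure is reproduced and is not in dispute.

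**Step 2: who would leave the SF-36 comparison under the literal reading.**

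| | Usual care | Enhanced therapy |
|---|---|---|
| With an ulcer | 63 × 0.37 = 23.3 | 63 × 0.15 = 9.45 |
| Remaining | 63 × 0.63 = 39.7 | 63 × 0.85 = 53.6 |

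About 33 of 126 participants (23.3 + 9.45 = 32.8) drop out of the outcome, unevenly by arm. The comparison becomes roughly 54 against 40.

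**Step 3: what the restriction removes.** In all randomised participants, the part of the SF-36 difference that comes from prevention is (0.37 − 0.15) × D = 0.22 × D. Among ulcer-free participants it is 0 by construction, whatever D is.

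**Step 4: what the unrestricted comparison could show.** Power with 63 per arm is approximately Φ(0.22 × D × √(63/2) − 1.96). It counts only results in favour of enhanced therapy, takes a common SD of 1 and makes no baseline adjustment:

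| Assumed D (SD) | Prevention component (SD) | Power |
|---|---|---|
| 0.25 | 0.055 | 5% |
| 0.50 | 0.110 | 9% |
| 0.75 | 0.165 | 15% |
| 1.00 | 0.220 | 23% |

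Analysing everyone gives an unselected estimate. It does not make a significant SF-36 result likely from prevention alone.

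**The case against.** The strongest reply is that the parenthesis only names instruments. A wound scale can be given only to people with a wound, SF-36 is the general questionnaire, and together the two halves of the phrase cover everyone. The collection schedule, the unsplit objective and the intention-to-treat rule all fit that reading, and no sentence expressly excludes participants with an ulcer from the SF-36 analysis. This may well be what was meant. It does not remove the point: the words pair SF-36 with the ulcer-free group, the next lines make the cited reference the definition, and the analysis section relies on that list. If only instruments were meant, the wording should say so.

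A reader might infer more: that no quality-of-life measure compares the randomised groups, so the trial cannot show the gain it promises. The documents do not support this. QALYs from EQ-5D-5L are on the same list. All participants receive EQ-5D-5L before each three-monthly visit, with one extra form 4 weeks after an ulcer. QALYs are compared between arms with no split by ulcer status, and they enter the primary cost-utility outcome.

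A reader might also infer that the ulcer-free remainder in usual care is healthier, which would tilt SF-36 against enhanced therapy. If ulcers struck exactly the highest-risk participants, mean risk among the ulcer-free would lie 0.599 SD (usual care) and 0.274 SD (enhanced therapy) below average. With an assumed correlation of 0.1 to 0.3 between higher risk and lower quality of life, the shift would be (0.599 − 0.274) × 0.1 to 0.3 = 0.03 to 0.10 SD. Both the extreme selection and the correlation are invented for illustration. The documents establish neither the size nor the direction.

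It is fair to add that baseline adjustment is a recommendation; the planned unadjusted test is not an error in itself.

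**Conclusion.** The point holds as a badly fixed definition of one secondary outcome. Followed as worded, the SF-36 comparison conditions on the primary clinical endpoint, loses about 23 of 63 usual-care and 9 of 63 enhanced-therapy participants, and excludes the prevention component of any SF-36 gain. It contradicts the article's own objective, collection schedule and intention-to-treat rule.

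The counts rest on the article's planning rates; actual numbers will follow observed recurrence. The value of 0.22 × D depends on an SF-36 loss that the documents do not give, but the zero in the ulcer-free group does not depend on it.

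No SF-36 data are missing by design, and the trial keeps an unsplit quality-of-life comparison through EQ-5D-5L and QALYs. This is a minor correction.

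**What to change.** In Outcomes {12}, replace the parenthesis with two separate entries:

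- SF-36 at 12 months, compared between arms in all randomised participants whether or not an ulcer recurred, adjusted for baseline SF-36.
- Cardiff Wound Impact Schedule at 4 and 12 weeks after an ulcer, reported descriptively in participants with an unhealed ulcer, with no between-arm claim.

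In Other study outcomes, exempt SF-36 from the general unadjusted test and name a linear model with arm and baseline SF-36. Baseline adjustment uses a measurement already taken and will usually sharpen the estimate.

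The cost is about one sentence in each place. No visit, questionnaire or participant is added. Settling it before analysis also removes a later choice between two populations that could give different answers.

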**Fig. 2 Fig2:**
[figure not shown]
Study design and main procedures for participants. All follow-up visits can deviate a maximum 2.5 weeks from the scheduled timepoint. * = An unscheduled visit becomes a scheduled visit when a participant develops an ulcer. This visit will be repeated every 3 months if an ulcer is not healed, which is the same frequency as normal follow-up visits. ‡ = Regular final visit will be at 12 months. However, if a participant has an ulcer at 12 months, there will be extra follow-up visits after the final visit. These will take place at 15 and 18 months or, if the ulcer has healed earlier, at 2 weeks after healing. The extra follow-ups follow the procedures of the unscheduled visit. ** = For enhanced therapy group only. † = the study questionnaire consists of a combination of multiple validated questionnaires, including adapted versions of the Monitor Orthopedic Footwear, treatment satisfaction questionnaire, COM-b (Capabilities, Opportunities, Motivations) questionnaire, and an assessment of knowledge about foot care based on the PIN questionnaire (Patients’ Interpretation of Neuropathy). ENROL, enrolment visit; BASE, baseline visit; RAND, randomization visit; FU_x_, follow-up visit (numbered by visit number); UV, unscheduled visit; FV, final visit; SF-36, quality of life questionnaire; EQ-5D-5L, quality of life questionnaire measuring quality-adjusted life years; iMTA, Institute for Medical Technology Assessment questionnaires on medical consumption and productivity costs; CWIS, Cardiff Wound Impact Schedule questionnaire

### Participant timeline {13}

Participants who consent to participate and who meet the in- and exclusion criteria will have a baseline visit for patient screening, physical examination, and other measurements (details provided in the “Data collection and management” section). In a next visit, participants will be randomly assigned to the enhanced therapy or usual care group. Each participant will be followed for 12 months or, in case of a foot ulcer present at the 12 months’ follow-up visit, up to a maximum of 18 months, the latter 6 months for foot ulcer monitoring only. Figure 2 shows an overview of the study design and participant timeline.

### Sample size {14}

Based on an analysis of RCTs that have recurrent foot ulcers in people with diabetes as outcome, a risk reduction in participants with one or more recurrent foot ulcers up to 75% can be expected from a state-of-the-art multimodal treatment approach [63]. Using a more conservative estimate, we expect a risk reduction of 59% for the enhanced therapy group compared to usual care. This is based on previous studies that show that footwear and at-home foot temperature monitoring interventions combined can achieve such effect sizes [2, 15, 63]. With an expected ulcer recurrence in 37% of the participants in usual care [2, 20], this 59% risk reduction leads to a hypothesized 15% ulcer recurrence rate in the enhanced therapy group. With 15% ulcer recurrence in enhanced therapy and 37% in usual care, *α* = 0.05 (two-sided) and power = 80%, enrolment ratio of 1, power calculations show that 122 participants are required (61 per study group). We expect no dropout or missing data for the intention-to-treat analysis of the clinical outcome based on previous trial experience that clinical outcome can be obtained in each participant [20], which means that a total 122 participants are required for the primary clinical outcome.

For footwear adherence as the primary patient-related outcome measure, we expect 71% (sd 25%) adherence in usual care at 12 months based on findings from previous research [10, 12]. We expect an increase in footwear adherence in the enhanced therapy group to a level of 85% at 12 months, through the effect of indoor footwear provision [12] and structured education. With *α* = 0.05 (two-sided) and power = 80%, enrolment ratio of 1, power calculations show that 100 participants are required (50 per study group). Including a drop-out rate of 20%, this leads to a sample size of 120 participants in total for the primary patient-related outcome.

For cost-utility as primary health-economic outcome measure, we anticipate a clinically relevant 0.1 gain in QALYs for the enhanced therapy group with group standard deviations for QALYs of 0.15 [64]. We use an estimation of cost difference of €0 per participant between both groups with group standard deviations for costs of €1000 [65, 66]. We allow room here for a more positive outcome in costs, as we predict an average cost saving per participant of €1113.75 for enhanced therapy based on the expected clinical effect of 59% relative reduction in number of ulcers compared with usual care (see Table 1). With a willingness to pay (WTP) of €50,000, a correlation between costs and QALYs (*ρ*) of 0, *α* = 0.05 (two-sided), power = 80%, and a drop-out rate of 20%, this leads to a sample size of 63 participants per study group, or 126 participants in total. Without drop-out, a sample size of (63 × 0.8 =) 51 participants per study group or 102 in total is required.

**Table 1 Tab1:** Average predicted costs per participant

				**Enhanced therapy**		**Usual care**	
**Modality**	**Event/activity**	**Time (hours)**	**Unit costs**	**Expected frequency**	**Expected costs**	**Expected frequency**	**Expected costs**
	Ulcer development [6]	-	€10,000	0.15	€1500	0.37	€3700
	Podiatrist	1	€100	0.50	€50	0.00	€0
Custom-made footwear	Optimization equipment: pressure measurements [36]	-	€50	1.00	€50	0.00	€0
	Shoe technician	1	€100	2.00	€200	0.00	€0
Custom-made indoor footwear	Production and optimization [13]	-	€400	0.95	€380	0.00	€0
Personalized temperature monitoring	Thermometry [38]	-	€75	0.75	€56.25	0.00	€0
Personalized education	Structured education	1	€100	0.50	€50	0.00	€0
	Motivational Interviewing	1	€100	2.00	€200	0.00	€0
	Equipment [49, 57]	-	€100	1.00	€100	0.00	€0
**Total**					€2,586.25		€3,700

Average of predicted additional costs per participant of enhanced therapy versus usual care, based on the expected frequencies as described in the power calculation. For all costs except ulcer development, usual care is used as index. Unit cost estimations are based on previous studies and standard hourly wages of a college educated professional in the Netherlands

With the power calculations showing a requirement of 122 participants for the primary clinical outcome, 120 for the primary patient-related outcome, and 126 for the primary health-economic outcome, a sample size of 126 participants provides adequate power for all three primary outcomes.

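### The adherence sample size is inflated for 20% drop-out by multiplying by 1.2; the requirement should read 125, not 120, and the planned 126 still covers it

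*Protocol article*

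**What the plan says.** All the figures are in the protocol article, Sample size {14}.

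**Footwear adherence.** The inputs are "we expect 71% (sd 25%) adherence in usual care at 12 months" and an "increase in footwear adherence in the enhanced therapy group to a level of 85% at 12 months". With alpha at "0.05 (two-sided) and power = 80%, enrolment ratio of 1, power calculations show that 100 participants are required (50 per study group"). The next step is "Including a drop-out rate of 20%, this leads to a sample size of 120 participants in total".

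**Cost-utility.** The inflated figure comes first: "a drop-out rate of 20%, this leads to a sample size of 63 participants per study group, or 126 participants in total". The section then works back: "Without drop-out, a sample size of (63 × 0.8 =) 51 participants per study group or 102 in total is required".

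**Summary.** The closing sentence of the section lists 122, 120 and 126 as the requirements for the clinical, adherence and health-economic outcomes, and concludes that "a sample size of 126 participants provides adequate power for all three primary outcomes". Recruitment {15} fixes enrolment at 126. Strengths and limitations and the Conclusion both rely on the trial being powered for all three outcomes.

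**The concern.** Drop-out is a fraction of those enrolled, so completers equal enrolled × (1 − drop-out), and the number to enrol is the number needed divided by (1 − drop-out). The adherence calculation multiplies by (1 + drop-out) instead, which always gives too small a number. The cost-utility calculation uses the division form, so the two are inconsistent as well.

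Footwear adherence is one of three primary outcomes, and its requirement of 120 is carried into the summary that supports the adequate-power statement. A reader sees a cushion of 6 participants between 120 and 126. If recruitment closed at, say, 120 to 124, the team could believe adherence was still covered at the assumed drop-out when it was not.

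**Working it through.** **Inputs (Sample size {14}):** means 71% and 85%, so a difference of 14 points; SD 25%, given for usual care and taken here for both groups; two-sided alpha 0.05; power 80%; 1:1 allocation; drop-out 20%; planned total 126.

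**1. The plan's figure before drop-out.** Normal approximation:

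n per group = 2 × [SD × (1.960 + 0.842) / difference]² = 2 × [25 × 2.802 / 14]² = 50.06.

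This reproduces the stated 50 per group (100 in total) to rounding.

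**2. The plan's figure after drop-out.** 100 × 1.2 = 120. The stated 120 is reproduced only by this multiplication.

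**3. What 120 delivers.** 120 × 0.8 = 96 completers, 48 per group. Put the other way, 120 enrolled retains 100 only if drop-out is no more than 1 − 100/120 = 16.7%.

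**4. The correct inflation.** 100 / 0.8 = 125. Per group, 50 / 0.8 = 62.5, so 63 per group or 126 with equal groups. Starting from the unrounded 50.06 gives 50.06 / 0.8 = 62.6, again 63 per group.

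**5. Power for adherence after 20% loss** (difference 14, SD 25, two-sided alpha 0.05):

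| Enrolled | Completers per group | t-test | Normal approximation |
|---|---|---|---|
| 120 | 48 | 77.5% | 78.3% |
| 125 | 50 | 79.2% | 80.0% |
| 126 | 50.4 | 79.5% | 80.3% |

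**6. Margin.** As printed: 126 − 120 = 6. Corrected: 126 − 125 = 1, or 126 − 126 = 0 with equal groups.

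**7. The rule used for cost-utility.** 63 × 0.8 = 50.4, printed as 51, and 50.4 / 0.8 = 63. The form is right. Only the rounded number fails to divide back: 51 / 0.8 = 63.75.

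**8. Does that rounding leave cost-utility short?** With a QALY gain of 0.1, QALY SD 0.15, cost difference €0, cost SD €1000, willingness to pay €50,000 and correlation 0:

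- Net-benefit difference = 50,000 × 0.1 = €5000.
- Net-benefit SD = √[(50,000 × 0.15)² + 1000²] = €7566.
- n per group = 2 × [7566 × 2.802 / 5000]² = 35.9, so 36, or 36 / 0.8 = 45 with drop-out.
- Power at 50.4 per group is about 91%.

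On the stated inputs, 126 is not short for cost-utility.

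**The case against.** The strongest reply is that nothing in the trial changes. Enrolment is set by the largest of the three requirements, 126; the corrected adherence figure is 125; and the 77.5% belongs to an enrolment of 120 that nobody plans. That stands, and it confines the point to a wrong stated figure and the margin a reader draws from it. It does not make 120 right, because the sentence before it requires 100 completers and 120 does not supply them at the stated drop-out.

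It can also be said that multiple imputation is the first choice for missing data, under the missing-data heading {20c}, so counting every drop-out as lost information is conservative. That is fair, but the plan itself chose to inflate for drop-out, and the inflation should then be done correctly.

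Three stronger readings are tempting and are not supported:

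- **That cost-utility needs 128.** A reader might take "51 participants per study group or 102 in total is required" and compute 51 / 0.8, rounded up to 64 per group. But the plan starts from 63, and the 51 is 50.4 rounded up, so the extra 2 participants come from rounding twice. The stated inputs need only about 36 per group before drop-out. That those inputs do not lead to 63 is a separate question, not a drop-out error.
- **That adherence needs 130.** An exact t-test passes 80% at 52 per group (80.7%), and 52 / 0.8 = 65 per group. But 51 per group already gives 79.97%. The difference is between normal and t formulas and has nothing to do with the drop-out rule.
- **That baseline adjustment would make up the power.** The article gives no correlation between baseline and follow-up adherence, and plans an unadjusted t-test, so no gain can be claimed.

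**Conclusion.** The adherence requirement is understated by 5: 125, not 120. The section applies one drop-out rate by two incompatible rules. At the printed 120, power would be 77.5% to 78.3% instead of 80%. At the planned 126 it is 79.5% to 80.3%, depending on the formula, so the trial's size remains adequate for adherence to within rounding, with essentially no margin. These figures assume an SD of 25% in both groups, a 14-point difference, and exactly 20% drop-out contributing no outcome information. The 51 per group for cost-utility is a rounding blemish and does not show a shortfall.

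**What to change.** In Sample size {14}:

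1. Replace 120 by 100/0.8 = 125 (63 per group, 126 with equal groups) in the adherence paragraph, and make the same change in the closing summary of the three requirements.
2. Add that 126 enrolled with 20% drop-out leaves about 50 per group, giving about 79.5% (t-test) to 80.3% (normal approximation) power for adherence, so the margin is 0 to 1 participants.
3. Print 63 × 0.8 as 50.4, or explain that 51 per group (102 in total) is that figure rounded up.

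The cost is a few words. Enrolment stays at 126 and the analysis is untouched; the only loss is that the stated margin for adherence becomes less favourable.
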